### **7.4 Collection and Reporting**

Adverse events can be spontaneously reported or elicited during open-ended questioning, examination, or evaluation of a subject. (In order to prevent reporting bias, subjects should not be questioned regarding the specific occurrence of one or more AEs.)

If known, the diagnosis of the underlying illness or disorder should be recorded, rather than its individual symptoms. The following information should be captured for all AEs: onset, duration, intensity, seriousness, relationship to study drug, action taken, and treatment required. If treatment for the AE was administered, it should be recorded on the appropriate CRF page. The investigator shall supply the sponsor and Ethics Committee with any additional requested information, notably for reported deaths of subjects.

Completion of supplemental CRFs may be requested for AEs and/or laboratory abnormalities that are reported/identified during the course of the study.

#### **7.4.1 Serious Adverse Events**

Following the subject's written consent to participate in the study, all SAEs must be collected, including those thought to be associated with protocol-specified procedures. All SAEs must be collected that occur within 70 days of discontinuation of dosing of the investigational products. If applicable, SAEs must be collected that relate to any later protocol-specified procedure (e.g., a follow-up skin biopsy).

The investigator should notify Fondazione NIBIT/CRO of any SAE occurring after these time periods that is believed to be related to study drug or protocol-specified procedure.

Serious adverse events, whether related or unrelated to study drug, must be recorded on the SAE page of the CRF and reported within 24 hours to Fondazione NIBIT (or designee) to comply with regulatory

requirements. An SAE report should be completed for any event where doubt exists regarding its status of seriousness.

All SAEs must be reported within 24 hours by confirmed facsimile transmission (fax) and mailing of the completed SAE page (top, white, original). In some instances where a facsimile machine is not available, overnight express mail may be used. If only limited information is initially available, follow-up reports are required. (Note: Follow-up SAE reports should include the same investigator term(s) initially reported.) In selected circumstances, the protocol may specify conditions that require additional telephone reporting. The SAE electronic CRF in the electronic data capture tool should not be used.

If the investigator believes that an SAE is not related to study drug, but is potentially related to the conditions of the study (such as withdrawal of previous therapy, or a complication of a study procedure), the relationship should be specified in the narrative section of the SAE page of the CRF.

If an ongoing SAE changes in its intensity or relationship to study drug, a follow-up SAE report should be sent within 24 hours to the sponsor. As follow-up information becomes available it should be sent within 24 hours using the same procedure used for transmitting the initial SAE report. All SAEs should be followed to resolution or stabilization.

Fondazione NIBIT/CRO should notify all SAE to Astex Farmacovigilance

***SAE FACSIMILE TRANSMISSION:***

Contact information for SAE Facsimile Transmission will be provided to each site at time of study initiation.

***SAE MAILING ADDRESS:***

Contact information for SAE mailing will be provided to each site at time of study initiation.

***7.4.2 Handling of Expedited Safety Reports***

In accordance with local regulations, Fondazione NIBIT/CRO will notify investigators of all SAEs that are suspected (related to the investigational product) and unexpected (i.e., not previously described in the Investigator Brochure). In the European Union (EU), an event meeting these criteria is termed a Suspected, Unexpected Serious Adverse Reaction (SUSAR). Investigator notification of these events will be in the form of an expedited safety report (ESR).

Other important findings which may be reported by the sponsor as an ESR include: increased frequency of a clinically significant expected SAE, an SAE considered associated with study procedures that could modify the conduct of the study, lack of efficacy that poses significant hazard to study subjects, clinically significant safety finding from a nonclinical (e.g., animal) study, important safety recommendations from a study data monitoring committee, or sponsor decision to end or temporarily halt a clinical study for safety reasons.

Upon receiving an ESR from Fondazione NIBIT/CRO, the investigator must review and retain the ESR with the Investigator Brochure. Where required by local regulations or when there is a central IRB/IEC for the study, the sponsor will submit the ESR to the appropriate IRB/IEC. The investigator and IRB/IEC will determine if the informed consent requires revision. The investigator should also comply with the IRB/IEC procedures for reporting any other safety information.

In addition, suspected serious adverse reactions (whether expected or unexpected) shall be reported by Fondazione NIBIT/CRO to the relevant competent health authorities in all concerned countries according to local regulations (either as expedited and/or in aggregate reports). The Fondazione NIBIT/CRO will also report all suspected serious adverse reactions to Astex Farmacovigilance, within 24 hours from being informed by study Investigators.

### **7.4.3 Non serious Adverse Events**

The collection of non-serious AE information should begin after patient's signed informed consent has been obtained. Non-serious AE information should also be collected from the start of a placebo lead-in period or other observational period intended to establish a baseline status for the subjects.

If an ongoing non-serious AE worsens in its intensity or its relationship to the study drug changes, a new non-serious AE entry for the event should be completed. Non-serious AEs should be followed to resolution or stabilization, or reported as SAEs if they become serious (see Section 7.1.1). Follow-up is also required for non-serious AEs that cause interruption or discontinuation of study drug, or those that are present at the end of study treatment as appropriate.

All identified non-serious AEs must be recorded and described on the appropriate non serious AE page of the CRF (paper or electronic).

## **7.5 Laboratory Test Abnormalities**

All laboratory test values captured as part of the study should be recorded on the appropriate laboratory test results pages of the CRF, or be submitted electronically from a central laboratory. In addition, the following laboratory abnormalities should also be captured on the non-serious AE CRF page (paper or electronic) or SAE paper CRF page as appropriate:

- Any laboratory test result that is clinically significant or meets the definition of an SAE
- Any laboratory abnormality that required the subject to have study drug discontinued or interrupted
- Any laboratory abnormality that required the subject to receive specific corrective therapy

It is expected that wherever possible, the clinical, rather than the laboratory term would be used by the reporting investigator (e.g., anemia versus low hemoglobin value).

## **7.6 Overdose**

An overdose is defined as the accidental or intentional ingestion or infusion of any dose of a product that is considered both excessive and medically important. All occurrences of overdose must be reported as an SAE (see Section 7.4.1 for reporting details.)

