### **1.3.5.3    *Overdose***

No event associated with overdose has been reported in any SGI-110 study to date. Standard supportive measures should be taken in the event of an overdose.

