## 1.5 Overall Risk/Benefit Assessment

In the clinical trials conducted to date, SGI-110 has shown antitumor activity with a manageable safety profile. The two main drug-related adverse reactions of SGI-110 are myelosuppression (neutropenia, febrile neutropenia, thrombocytopenia, and anemia) and injection-site events such as pain, irritation, and inflammation. At the SGI-110 doses and schedule proposed in this study (15-60 mg/m^2 day on Days 1-5), there have been no reports of drug-related myelosuppression in MDS and AML subjects in study SGI-110-01. The starting dose of 30 mg/m^2 day on Days 1-5 is 33% of the MTD for single-agent treatment with SGI-110. However, SGI-110 is generally administered in 28 day cycles and in this study will be administered in 21 day cycles. Despite the lack of overlapping toxicity with ipilimumab, the conservative starting dose and opportunity for de-escalation are in place for that reason.

Pain and burning at the injection site has been reported that are related to dose and volume of injection. These AE are Grade 1 and easily managed with icing of the site before and after injection. Other than these events described above, SGI-110 has been well tolerated up to 90 mg/m^2 day x5 and 125 mg/m^2 weekly x3 in 28 day cycles. For more detailed information, please refer to the IB for SGI-110.

The anti-CTLA-4 mAb ipilimumab, improves survival of metastatic melanoma with a well-known safety profile; the most common treatment-related AEs in subjects who received ipilimumab 3 mg/kg were irAEs affecting the skin and GI tract (eg, pruritus, rash, and diarrhea). Established treatment guidelines are actually available to safely manage the immune-related Adverse Events related to ipilimumab. For more detailed information, please refer to the IB for ipilimumab. The safety profile of SGI-110 in combination with ipilimumab will be tested for the first time in this trial, however due to the different nature of two compounds no overlapping toxicity will be expected. Evidences generated with SGI-110 in vivo demonstrated that besides having a direct activity on tumor growth as a single agent, SGI-110 was able to “sensitize” neoplastic cells to the anti-tumor activity of CTLA-4 blockade, improving its efficacy.

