### ***5.2.1 Dosage and Administration***

#### ***SGI-110 schedule***

SGI-110 will be administered:

Start at 30 mg/m^2 day s.c. on W0, 3, 6, 9 Day 1 - 5 q21 days. Dose Level -1: 15 mg/m^2 day; dose level +1: 45 mg/m^2 day, Dose Level +2: 60 mg/m^2 day for a total of 4 cycles.

SGI-110 is administered by SC injection preferably in the abdominal area; however the thigh and arms may be used. A Luer-Lok disposable syringe should be used when dispensing and administering SGI-110. Due to the slightly viscous nature of the preparation, use of thin-walled subcutaneous needle is highly recommended for ease of subcutaneous administration and subject comfort. SGI-110 should be injected slowly (up to one minute) as some injection site discomfort or pain may be experienced.

If injection site pain is reported upon injection, apply ice packs to the injection site both before and after injection. If the injection site events are reported at subsequent injections despite slow injection and the use of ice packs, pre-treatment with topical or systemic analgesics can be considered. The total amount (in mg) of SGI-110 to be administered will be determined based on the body surface area (BSA). In calculating the BSA, actual heights and weights taken at enrolment should be used. There will be no adjustments to “ideal” body weight or dose modifications related to changes in body weight < +/- 10%. The institutional standard for calculating BSA is acceptable.

The site(s) of SGI-110 SC injections will be captured on the dosing CRF.

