### ***5.3.1 Dose Modifications***

During dose escalation, the dose of SGI-110 to be administered is determined by the dose level and the subject's body weight at consent. Thereafter, it will be determined by the MTD and the subject's body weight. Once a dose of SGI-110 is established, it should be maintained unless the subject's body weight decreases by 10% or a safety issue requires dose reduction. If a myelosuppressive DLT occurs, the patient may resume at the next lower dose level of SGI-110 after recovery of counts.

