### ***6.3.1 Medical History, Physical Exam, Physical Measurements***

A detailed Medical History will be obtained at Screening. Medical history must include date of diagnosis, including histological or cytological documentation of malignancy. Any toxicity related to previous treatments should be mentioned, if applicable.

A complete physical examination including subject's height and weight will be performed at Screening. Prior to dosing (within 3 days), the subject's weight must be obtained to calculate the ipilimumab dose and the subject's body surface area on which SGI-110 dose is calculated.

If the Screening physical exam is conducted within 24 hours of dosing on Week 0, then a single examination may count as both Screening and Pre-dose examination. Subsequent physical exams will be performed if clinically indicated. Any physical examination finding that qualifies as an AE or SAE must be documented on the appropriate CRF pages. Pre-treatment events present within 2 weeks of starting therapy, whether or not related to current disease, will be captured prior to the study start. Any worsening ( $\geq 1$  Grade from Baseline) will be documented as an AE in the CRF.

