#### 7.1.1 *Serious Adverse Events*

A serious AE (SAE) is any untoward medical occurrence that at any dose:

- results in death,
- is life-threatening (defined as an event in which the subject was at risk of death at the time of the event; it does not refer to an event which hypothetically might have caused death if it were more severe),
- requires inpatient hospitalization or causes prolongation of existing hospitalization (see note below for exceptions),
- results in persistent or significant disability/incapacity,
- is a congenital anomaly/birth defect ,
- is an important medical event (defined as a medical event(s) that may not be immediately life-threatening or result in death or hospitalization but, based upon appropriate medical and scientific judgment, may jeopardize the subject or may require intervention [e.g., medical, surgical] to prevent one of the other serious outcomes listed in the definition above.) Examples of such events include, but are not limited to, intensive treatment in an emergency room or at home for allergic bronchospasm; blood dyscrasias or convulsions that do not result in hospitalization).

Suspected transmission of an infectious agent (e.g., any organism, virus or infectious particle, pathogenic or non-pathogenic) via the study drug is an SAE and must be reported accordingly.

Although overdose and cancer are not always serious by regulatory definition, these events should be reported on an SAE form and sent to Fondazione NIBIT/CRO that will forward to BMS in an expedited manner.

All pregnancies, regardless of outcome, must be reported to the sponsor on a Pregnancy Surveillance Form, not an SAE form (see Section 7.7).

NOTE:

The following hospitalizations are not considered SAEs in Fondazione NIBIT clinical studies:

- a visit to the emergency room or other hospital department < 24 hours, that does not result in admission (unless considered "important medical event" or event life threatening),
- elective surgery, planned prior to signing consent,
- admissions as per protocol for a planned medical/surgical procedure,
- routine health assessment requiring admission for baseline/trending of health status (e.g., routine colonoscopy),
- medical/surgical admission for purpose other than remedying ill health state and was planned prior to entry into the study. Appropriate documentation is required in these cases,

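### The Study Schema in 4.1.4 prints all four SGI-110 dose levels in mg/kg where the rest of the protocol has mg/m2, and 5.3.1 adds to the conflict by naming body weight as the dose basis

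*Combined protocol and SAP*

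**What the plan says.** **Dose unit.** The table in 4.1.4 lists four cohorts. Its SGI-110 column shows 15, 30, 45 and 60 mg/kg s.c. for Levels -1, 0, +1 and +2, and its ipilimumab column shows 3 mg/kg i.v. throughout. Everywhere else that the four levels are set out (synopsis, 4.1.1, 4.1.5, 5.2.1, 5.2.2, 8.1) the same numbers are in mg/m2.

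**Dose basis.** Section 5.2.1 determines the SGI-110 amount in mg from BSA. Section 6.3.1 has weight measured before dosing to obtain the ipilimumab dose and the "body surface area on which SGI-110 dose is calculated". Section 5.3.1 says that during escalation "the dose of SGI-110 to be administered is determined by the dose level and the subject's body weight at consent", and that afterwards it depends on the MTD and body weight. It does not mention BSA.

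**Overdose.** Section 7.6 begins "An overdose is defined as the accidental or intentional ingestion or infusion of any dose of a product", limits the term to doses judged excessive and medically important, and makes every overdose reportable as an SAE. On route, 5.2.1 says "SGI-110 is administered by SC injection preferably in the abdominal area". Section 7.1.1 says "Although overdose and cancer are not always serious by regulatory definition, these events should be reported on an SAE form", and names no route. Section 7.4.1 requires an SAE report for "any event where doubt exists regarding its status of seriousness". Section 1.3.5.3, in the SGI-110 safety summary, says "No event associated with overdose has been reported in any SGI-110 study to date".

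**The concern.** The primary objective is the MTD of SGI-110, so the dose level is the quantity that the trial is about. A schema is the table a reader goes to for the dose levels. Here its unit for the escalated drug contradicts the dosing section. Nothing in the table reveals the slip, because the ipilimumab column beside it is correctly in mg/kg. Section 5.3.1 points the same way, so the weight-based reading appears in two places.

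At stake is a protocol that states its dose levels consistently, and a schema that can be copied into pharmacy sheets, training slides or a report without carrying the error along.

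The overdose wording is a smaller matter of the same kind. The only definition of overdose in the protocol names two routes. Neither is the route of the escalated drug, and nothing in this trial is ingested.

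**Working it through.** **1. Which unit is intended?**

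| Place | SGI-110 levels or basis | Unit |
|---|---|---|
| 4.1.4 Study Schema | 15 / 30 / 45 / 60 | mg/kg |
| Synopsis, 4.1.1, 4.1.5, 5.2.1, 5.2.2, 8.1 | 15 / 30 / 45 / 60 | mg/m2 |
| 1.5 | range 15-60, start 30 | mg/m2 |
| 5.2.1, 6.3.1 | basis is BSA | mg/m2 implied |
| 5.3.1 | basis given as body weight | none given |

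Section 1.5 settles the matter directly, because it writes the starting dose in mg/m2. A cross-check agrees. The same section says that the starting dose "is 33% of the MTD for single-agent treatment with SGI-110", and 1.3.2 gives a daily x5 MTD of 90 mg/m2/day in MDS: 30 / 90 = 0.333. The 90 applies to MDS only; in AML the MTD was not reached up to 125 mg/m2. So mg/kg in 4.1.4 is an error and not an alternative regimen.

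**2. Is 5.3.1 a separate weight-based rule?** No. Dose levels are defined in mg/m2 in 5.2.2, so weight can enter only through BSA, as 6.3.1 shows. The sentence is incomplete, and beside the schema it is misleading.

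**3. Size of the printed conflict.** The ratio of the two readings is the same at every level:

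(d mg/kg x weight) / (d mg/m2 x BSA) = weight / BSA

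The documents give no body sizes, so the weights and heights below are assumptions. BSA is taken as sqrt(kg x cm / 3600) (Mosteller, also assumed, since 5.2.1 allows the institutional standard).

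| Assumed body size | BSA (m2) | Level 0 at 30 mg/m2 | Level 0 at 30 mg/kg | Ratio |
|---|---|---|---|---|
| 50 kg, 155 cm | 1.47 | 44 mg | 1,500 mg | 34.1 |
| 70 kg, 170 cm | 1.82 | 55 mg | 2,100 mg | 38.5 |
| 100 kg, 185 cm | 2.27 | 68 mg | 3,000 mg | 44.1 |

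**4. Would the literal reading be noticed?** Section 5.1.4 describes 100 mg vials reconstituted to at most 100 mg/mL. For the 70 kg case, 2,100 / 100 = 21 vials and at least 21 mL in one day, against 1 vial and about 0.55 mL (55 / 100) for 30 mg/m2. The literal dose would be conspicuous at dispensing.

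**5. Overdose wording.** Ipilimumab is infused, so 7.6 covers it. SGI-110 is injected under the skin, which is neither ingestion nor infusion, so read literally 7.6 leaves it out. Section 7.1.1 asks for overdose on an SAE form whatever the route but does not define the term. Section 1.3.5.3 uses the word for SGI-110, so the protocol's own usage includes it. The only case left unclear is a medically important subcutaneous overdose without symptoms. There, 7.1.1 still asks for the form, and 7.4.1 favours reporting when seriousness is in doubt. The documents give no basis for a frequency.

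**The case against.** The strongest reply is that these are editorial slips without consequence. The sections that govern dosing (5.2.1, 5.2.2) are correct and repeat mg/m2. The e-Clinical system assigns the dose level, trained staff give the drug, and there is one centre. A literal mg/kg dose would expose itself by the number of vials. Four wrong entries are one typing error repeated. In 5.3.1, a level already expressed in mg/m2 leaves weight no role except through BSA. DLTs are defined by toxicity and not by overdose, so 7.6 has no bearing on escalation.

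Most of this stands, and it limits the point. A reader might infer from the fold difference that patients are likely to be misdosed. The documents do not support that, for the reasons just given. A reader might also infer from 7.6 that a subcutaneous SGI-110 overdose would go unreported. That does not follow either, given 7.1.1 and 7.4.1.

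What does not stand is the step from unlikely harm to no need for correction. The error is in the investigational plan and not in background text, it concerns the escalated drug, a second section leans the same way, and the right unit is beyond dispute.

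**Conclusion.** The 4.1.4 schema is wrong as written: all four SGI-110 levels carry mg/kg where mg/m2 is meant, and 5.3.1 reinforces the conflict. This conclusion rests on the text alone. The 34- to 44-fold figure rests on assumed body sizes and an assumed BSA formula. It measures how far apart the two printed units are and not any expected harm.

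The correction should be made at the next amendment. Neither the sample size, the escalation rule, the MTD definition nor any analysis is affected. The 7.6 wording is a minor consistency edit that would not justify an amendment by itself.

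**What to change.** - **4.1.4:** change mg/kg to mg/m2 for the four SGI-110 levels. Leave ipilimumab at 3 mg/kg.
- **5.3.1:** state that the SGI-110 dose is determined by the dose level (later the MTD) and BSA, as in 5.2.1 and 6.3.1, with weight as an input to BSA.
- **7.6 (minor):** replace ingestion or infusion with administration by any route, and keep the existing threshold that the dose be both excessive and medically important.

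The cost is a few words in three sections at the next amendment. No procedure, visit or reporting step is added. Any site material already copied from the schema should be checked for the same unit.

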## **7.7 Pregnancy**

Sexually active WOCBP must use an effective method of birth control during the course of the study, in a manner such that risk of failure is minimized (See Section 4.2.1 for the definition of WOCBP).

Before enrolling WOCBP in this clinical study, investigators must review the sponsor-provided information about study participation for WOCBP. The topics include the following:

- General Information
- Informed Consent Form
- Pregnancy Prevention Information Sheet
- Drug Interactions with Hormonal Contraceptives
- Contraceptives in Current Use
- Guidelines for the Follow-up of a Reported Pregnancy

Prior to study enrollment, WOCBP must be advised of the importance of avoiding pregnancy during study participation and the potential risk factors for an unintentional pregnancy. The subject must sign an informed consent form documenting this discussion.

